### Primary study parameter(s)

cfDNA methylation profiles and the summary score will be compared between patients with and without pathological response to CRT and, additionally, we will investigate associations between the cfDNA methylation profile/summary score, clinical, and molecular characteristics of the tumour. To obtain the most optimal panel of methylation markers predicting pathological response to CRT, we will perform adaptive group-regularized logistic ridge regression followed by post hoc group-weighted elastic net feature selection as described before [18]. In this innovative method group-regularisation of all markers is based on auxiliary data that is provided separately to the model resulting in improved marker selection. In our case this auxiliary data will consist of tissue-based comparison measures like fold changes in DNA methylation and RNA expression between patients with and without a pathological response. When sufficiently promising a targeted assay can be developed for the most optimal marker panel to reduce costs and facilitate future clinical implementation pending external validation of our findings. When available for the selected markers we will use publicly available data for this purpose and otherwise we will contact our network to find/collect a suitable sample cohort.

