### Study procedures

Patients with locally advanced rectal cancer scheduled to receive pre-operative chemo-radiation therapy (CRT) in the Erasmus MC will be informed about the study by the local investigator or local study coordinator. From 75 consenting patients, blood (2 × 10 ml) will be collected in cell-stabilizing blood collection tubes at 4 time points: [1] After diagnosis and before start with CRT, [2] between 1 and 2 weeks after treatment, [3] 0–3 days before surgery, and [4] between 2 and 5 weeks after surgery at the outpatient clinic visit. Blood will be collected at time points 3 and 4 for translational research. Of note, most patients (including the involved patient representatives) do not consider additional blood draws as a burden. We will ensure blood draws for the current project will coincide with hospital visits as much as possible. Next to the blood sampling we will also retrieve the formalin-fixed paraffin-embedded (FFPE) tissue biopsy obtained at diagnosis from the pathology archive for participating patients to allow comparative analyses between blood and tumour tissue. Clinical (TNM stage, tumour location, age, gender), pathological (differentiation grade, MSI status, TRG), and follow up (RFS and OS) data will be collected for all participating patients from the electronic patient files. Information about pathology material will be stored in databases from IKNL, CBS and PALGA and can be used for further information in the future. Obtained molecular results will not be communicated with the participating patients on an individual basis as this may cause unnecessary anxiety, but overall study results will be shared.

Blood will be processed into plasma within 96 h and stored at -80 degrees, according to our standard pipeline. cfDNA will be isolated from of the stored plasma, quantified, and quality will be evaluated using standard laboratory techniques.

Similarly, we will isolate RNA and DNA from diagnostic FFPE-tissue sections and evaluate the quantity and quality.

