MeD-seq analysis will be done on 10 ng cfDNA from the pre-treatment sample (baseline) and after 1 week of treatment as well as on genomic DNA from the tissue specimens as described before [6, 7]. In short, DNA will be digested with LpnPI yielding 32 bp fragments around the fully methylated recognition site containing a CpG. Samples will be prepped and purified for sequencing. Multiplexed libraries will be sequenced for ~ 20 M single reads. Tissue-based MeD-seq profiles will be used to determine the most informative regions for radio-sensitivity.

RNAseq analysis will be performed on RNA isolated from the FFPE tissue specimens, which has already been successfully performed in other, technically comparable, sample cohorts (unpublished data). RNAseq data will be used to determine genes associated with radio-sensitivity and, in addition, baseline molecular characteristics of the tumour, such as hypoxia, proliferation state of the tumour [8], and the consensus molecular subtype (CMS) [9] can be inferred from this data.

For RNAseq data, raw sequencing data will be mapped to the reference genome (GRCh38) using the STAR aligner after which the duplicate reads are marked using Sambamba. Next, FeatureCounts will be used to obtain read counts for each gene. These read counts will be normalized using GeTMM to obtain the gene expression levels that can be used for downstream analyses, such as hypoxia and proliferation scores [8], as well as consensus molecular sutype (CMS) calling [9].

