For MeD-seq data, processing is carried out using specifically created scripts in Python, which include a trimming step to remove the Illumina adapters and a filtering step based on LpnPI restriction site occurrence between 13 and 17 bp from the 5’- or 3’ end of the read. Reads passing the filter are mapped to the genome using Bowtie 2. Using all unambiguously mapped reads count scores will be assigned to each individual LpnPI site in the genome. From genome-wide individual LpnPI site scores count scores are generated for 2 kilobase regions surrounding all known transcription start sites using a sliding window approach. To normalize potential differences in sequencing yields, regional read counts are divided by the total read count per sample. To generate a summary cfDNA methylation score, Z scores relative to healthy control samples (data already available from data of anonymous patients who donated blood at Sanquin and gave informed consent) will be calculated for every TSS region, which we will square and sum into a genome-wide Z score.

cfDNA methylation profiles and the summary score will be compared between patients with and without pathological response to CRT and, additionally, we will investigate associations between the cfDNA methylation profile/summary score, clinical, and molecular characteristics of the tumour.

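### The tissue fold changes that weight the cfDNA markers use the same patients and response labels as the model; unless computed on training patients only, they bias cross-validated panel accuracy upward

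*Protocol article*

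**What the plan says.** Four statements in the Protocol article fix the inputs.

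- **Whose tissue.** The investigators will "retrieve the formalin-fixed paraffin-embedded (FFPE) tissue biopsy obtained at diagnosis from the pathology archive for participating patients" (Study procedures).
- **Which contrast.** The auxiliary data are "tissue-based comparison measures like fold changes in DNA methylation and RNA expression between patients with and without a pathological response" (Primary study parameter(s); repeated under Statistical analysis). That contrast is the outcome the cfDNA model has to predict.
- **How it enters.** In the method, "group-regularisation of all markers is based on auxiliary data that is provided separately to the model". The model is "adaptive group-regularized logistic ridge regression followed by post hoc group-weighted elastic net feature selection".
- **Second use of the tissue.** "Tissue-based MeD-seq profiles will be used to determine the most informative regions for radio-sensitivity" (Study procedures).

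On the consequence, Primary study parameter(s) says: "When sufficiently promising a targeted assay can be developed for the most optimal marker panel". It makes later clinical use conditional on external validation, in public data where these exist for the selected markers and otherwise in a cohort still to be found. The parallel paragraph under Statistical analysis omits that condition. Objectives calls the study exploratory. No independent tissue cohort is named for the auxiliary data.

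**The concern.** A patient's response label contributes to the tissue fold changes. Those set the penalties and the region choice, and the penalised model then predicts that same patient. If the fold changes are fixed on the whole cohort before resampling, leaving a patient out of the cfDNA fit does not take that patient's label out of the penalties. Cross-validation, the usual protection when markers far outnumber patients, then no longer protects.

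At stake is the study's own answer on whether a marker panel predicts response, and the decision to develop a targeted assay, which that answer would inform.

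**Working it through.** **1. The only planning figure used.** The article states no panel accuracy to reproduce. The simulations use its 64 evaluable patients. That number follows if the unstated base response rate is taken as 0.25, so 0.625 after the 2.5-fold difference, with two-sided alpha 0.05, power 0.80 and 1:1 groups:

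- uncorrected n = [1.960·√(2·0.4375·0.5625) + 0.842·√(0.25·0.75 + 0.625·0.375)]² / 0.375² ≈ 26.3 per group
- continuity-corrected n = (26.3/4)·[1 + √(1 + 4/(26.3·0.375))]² ≈ 31.4, so 32 per group and 64 in total

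Expected responders are 32·0.25 + 32·0.625 = 28. This calculation concerns the high/low comparison. It supplies n for the check and has no other bearing on the point.

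**2. Why leaving patients out does not remove the label.** Let D be the responder-minus-non-responder mean difference in tissue for one region, and let ρ be the tissue–cfDNA correlation. With no true signal and folds balanced on response:

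- E[D in held-out patients | D in all patients] = D in all patients
- E[D in held-out patients | D in training patients] = 0

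In cfDNA the first becomes ρ·D. With 28 and 36 patients and unit variance, SE(D) = √(1/28 + 1/36) = 0.252. The top 1% of regions by |D| therefore have |D| of at least about 2.576·0.252 = 0.65. At ρ = 0.3, held-out cfDNA carries an expected spurious difference of at least 0.3·0.65 = 0.195 SD in each of 50 regions (1% of 5,000). At ρ = 0 there is none.

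**3. Simulation inputs.**

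- From the article: n = 64, and a model with group penalties and feature selection.
- Assumed: 28 responders; 5,000 regions, because the article gives no count for its "2 kilobase regions surrounding all known transcription start sites using a sliding window approach"; and ρ from 0 to 0.7. The Discussion says tumour-derived methylation is detectable in blood, which implies ρ above 0 but gives no size.
- No region is related to response, so the true AUC is 0.50. Cross-validation is 8-fold. All models are simplified stand-ins for the named method.

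**4. Mean cross-validated AUC with fold changes fixed on all patients.**

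| Model | ρ = 0 | 0.1 | 0.2 | 0.3 | 0.5 | 0.7 |
|---|---|---|---|---|---|---|
| A. Weights graded by rank of absolute fold change, kernel ridge (120 runs) | 0.49 | – | 0.69 | 0.85 | 0.99 | – |
| B. Top 1% of regions (120 runs; a 50-run repeat in brackets) | 0.50 | – | 0.62 (0.58) | 0.72 (0.70) | 0.88 (0.90) | – |
| C. Ten groups, weights learned from training cfDNA, ridge only | 0.50 | 0.53 | 0.65 | 0.83 | 0.996 | – |
| D. 10 / 50 / 200 groups, weights learned from cfDNA, ridge, then 20 markers selected (60 runs) | 0.494 / 0.510 / 0.495 | 0.499 / 0.503 / 0.515 | – | 0.622 / 0.599 / 0.555 | 0.662 / 0.751 / 0.715 | 0.642 / 0.812 / 0.842 |

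With fold changes recomputed on training patients only, the mean is 0.49–0.51 (A, B), 0.49–0.52 (C) and 0.48–0.53 (D) across all ρ. With fold changes taken from other patients, a run of model D's type gives 0.46–0.52.

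In model D, the share of null data sets reaching a cross-validated AUC of 0.70 is 3–5% at ρ = 0, 17–28% at 0.3, 37–65% at 0.5 and 30–95% at 0.7.

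**5. Sensitivity.** For model D's type with 20,000 regions (15 runs only, simulation SE 0.015–0.029), the fixed-on-all values are 0.58, 0.58, 0.65, 0.60 and 0.63 at ρ = 0.1, 0.2, 0.3, 0.5 and 0.7. So the leak is present but does not rise steadily with ρ. In-fold values are 0.48–0.52.

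**6. Control.** In model D the resubstitution AUC (fit and score on the same patients) is 0.993–0.999 with the tissue data and 0.997–0.999 without. That optimism comes from having far more markers than patients. Only the excess in step 4 is specific to the tissue data.

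**The case against.** The strongest reply is that the article describes no cross-validation, no accuracy measure and no order of computation. Saying the auxiliary data are supplied separately does not say they are computed once on everyone, and internal validation may sit in a fuller plan. This stands as far as it goes. A reader might infer that following the plan must give a biased answer, and the text does not establish that. What the text does fix is the tissue source, the label and the separate route into the model. Those choices would undermine ordinary cross-validation unless handled inside the folds.

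Other stronger readings are also unsupported:

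- **That the tissue data are why apparent accuracy would look near perfect.** Step 6 shows the same without them.
- **That the method requires auxiliary data independent of the labels.** Nothing in the article says so, and in-fold computation uses the training labels and is still unbiased for held-out patients. The requirement is separation of held-out patients.
- **That the whole primary analysis is circular.** The genome-wide summary score is a sum of squared Z scores against healthy controls. It uses neither tissue nor response labels, so its comparison between responders and non-responders is untouched.
- **That a false panel would reach patients.** The study is exploratory, without clinical consequences for participants, and external validation is named before clinical implementation. It would expose a false panel, but it would not correct the accuracy this study reports or the earlier decision that a panel is worth an assay.
- **That the RFS and OS Cox models are biased.** The panel is selected on response, those analyses are labelled exploratory, and no bias in them was shown.

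The Discussion also notes that separating ctDNA from total cfDNA is the challenge, so a high correlation across all regions cannot be presumed.

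**Conclusion.** The point holds conditionally. The auxiliary data and the region selection share patients and labels with the cfDNA model. If they are fixed on all patients, cross-validated panel accuracy is biased upward.

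With 64 patients, 5,000 regions and no true signal, the AUC rises from 0.50 to about 0.50–0.53 at a correlation of 0.1 or below, 0.56–0.85 at 0.3, and 0.66 to over 0.99 at 0.5. The upper ends come from graded weights or ridge without marker selection. The model with a selection step gives the lower ends. The short 20,000-region run falls partly outside these ranges (0.58 at 0.1, 0.60 at 0.5), so they are indicative only. The direction of the bias and its removal by in-fold computation are consistent across the models. The size rests on an assumed correlation, region count and simplified model.

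This should be fixed before analysis. It does not invalidate the study.

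**What to change.** In Study procedures (the MeD-seq region selection), Statistical analysis and Primary study parameter(s), state one of two things:

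- tissue fold changes, choice of informative regions, group penalties and elastic-net selection are all recomputed from training patients only within every resampling fold, so that held-out patients contribute neither tissue nor label; or
- the auxiliary data come from patients outside this cohort.

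State also that any reported panel accuracy, and the judgement that a panel is promising enough for a targeted assay, rest on that out-of-fold estimate. The final panel may still be fitted once on all patients, with the out-of-fold figure describing the procedure that produced it.

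The in-fold option needs no extra patients or samples. It costs computing time, and the reported accuracy is likely to be less favourable. The second option needs a suitable external tissue cohort. A confidence interval, a calibration report and out-of-fold scores in the RFS and OS models would be sensible additions, but they are optional and not part of this error.

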### Secondary study parameter(s)

In an exploratory analysis we will investigate whether the obtained methylation profiles are associated with our secondary outcome measures Recurrence Free Survival (RFS) and Overall Survival (OS). For this purpose we will perform univariate Cox regression analyses with the resulting methylation summary score for the entire profile as well as the selected marker panel (both continuous and dichotomized on the median). In case of significance (p < 0.1) for the univariate analysis subsequently a multivariate model will be built using known risk factors, including clinical (TNM stage, tumour location, age, gender), and pathological (differentiation grade, microsatellite instability status, TRG) parameters.

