### Sample size calculation

To detect a 2.5 fold difference in the chance of responding to CRT between circulating tumour DNA methylation high and - low patients with an alpha of 0.05 and a beta of 0.8, we need to include at least 64 patients according to the Chi-squared statistic with the continuity correction applied to compare proportions with a dichotomous outcome between two samples (http://www.sample-size.net/sample-size-proportions/). Based on previous and on-going studies we expect ~ 15% dropout due to either technical failure or loss to follow up. Therefore we will aim to include 75 patients in this project.

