### Statistical analysis

All main analyses will be performed according to the intention to treat principle using appropriate statistical software, such as R Project for Statistical Computing version 4.0.4. (https://www.r-project.org/) and SPSS version 21.0 (SPSS inc., Chicago, IL). ctDNA methylation levels will be scored high/low relative to the median value in the cohort. Missing samples will not be replaced, because a dropout rate taken into account in the sample size calculation.

We will perform adaptive group-regularized logistic ridge regression followed by post hoc group-weighted elastic net feature selection as described before [10]. In this innovative method group-regularisation of all markers is based on auxiliary data that is provided separately to the model resulting in improved marker selection. In our case this auxiliary data will consist of tissue-based comparison measures like fold changes in DNA methylation and RNA expression between patients with and without a pathological response. When sufficiently promising a targeted assay can be developed for the most optimal marker panel to reduce costs and facilitate clinical implementation.

Obtained data from patients following a watch and wait approach due to a sustained clinical response will be analysed as a separate subgroup since in these patients no pathological response can be determined. These patients will also follow the regular follow-up and will be analysed conform the other patients, only as a subgroup.

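### The marker panel is selected on pathological response and then tested univariately against RFS and OS in the same patients; with an in-sample panel score, that test largely re-tests response

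*Protocol article*

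**What the plan says.** - **Building the panel (Protocol article, Primary study parameter(s)).** The group-regularized ridge and elastic net procedure is run "To obtain the most optimal panel of methylation markers predicting pathological response to CRT". The auxiliary data that steer it, tissue fold changes in methylation and expression, are also contrasts between responders and non-responders.
- **Candidates (Study procedures).** Counts are formed for 2 kb windows around all known transcription start sites. The only summary score defined there is a sum of squared Z scores against healthy controls.
- **Survival analysis (Secondary study parameter(s)).** Univariate Cox models for RFS and OS are fitted "with the resulting methylation summary score for the entire profile as well as the selected marker panel (both continuous and dichotomized on the median"). A univariate p < 0.1 is labelled significance and leads to a multivariate model whose covariates, described as known risk factors, include "pathological (differentiation grade, microsatellite instability status, TRG) parameters". The analysis is called exploratory.
- **Patients (Study procedures).** RFS and OS are collected for every participant, so the cohort that builds the panel also supplies the survival data.
- **Watch-and-wait patients (Statistical analysis).** They have no pathological response and are analysed as a separate subgroup.

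The article does not say whether the panel score in the Cox model is a fitted weighted score or a sum of squares, or whether it is in-sample or cross-validated.

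**The concern.** A Cox p-value treats the covariate as fixed without reference to the patients' outcomes. A panel chosen from a very large number of regions in about 64 patients, and scored in those same patients, will separate responders from non-responders even when no region carries information. Such a score stands in for the response label. The univariate question of whether methylation is associated with RFS or OS then becomes whether response is associated with RFS or OS. The article itself treats TRG as a known risk factor, so a positive answer to the second question is to be expected.

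The study could therefore report a univariately significant blood panel for recurrence or death that has only recovered TRG. The panel could also appear to outperform the genome-wide score merely because it was tuned to response.

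**Working it through.** **1. The plan's own sample size, to fix the setting.** The inputs are "To detect a 2.5 fold difference in the chance of responding to CRT", "with an alpha of 0.05 and a beta of 0.8" (beta read as power 0.80), "Chi-squared statistic with the continuity correction applied", and equal groups because "ctDNA methylation levels will be scored high/low relative to the median value in the cohort". The response rates are not given. With 25% v 62.5% (ratio 2.5, mean 43.75%), two-sided:

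- Uncorrected: n = [1.960·√(2·0.4375·0.5625) + 0.842·√(0.25·0.75 + 0.625·0.375)]² / 0.375² = 26.3 per group.
- Continuity-corrected: (26.3/4)·[1 + √(1 + 4/(26.3·0.375))]² = 31.4, so 32 per group and 64 in total.

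This matches "we need to include at least 64 patients". Dividing by 0.85 gives 75.3, against 75 planned. So 64 evaluable patients is the right size for the check.

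**2. Simulation under pure noise.** There are 64 patients, and 2,000 independent noise markers unrelated to response or survival. A ridge fit to response keeps 20 markers and refits them, standing in for the cited method. Half of the patients respond, and survival depends on response only. The hazard ratio (HR, responder v non-responder), event count, marker count and panel size are assumptions, because the article gives none of them. There were 600 runs per setting with likelihood-ratio Cox tests. The in-sample score correlates about 0.89 with response.

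Share of noise panels with univariate p < 0.1 (continuous score, nominal 10%), beside the power of response itself at alpha 0.1, Φ(√(d·0.25)·|ln HR| − 1.645) for d events:

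| HR | Panel, 16 / 24 events | Response itself, 16 / 24 events |
|---|---|---|
| 1.0 | 11% / 10% | – |
| 0.7 | 16% / 19% | – |
| 0.5 | 34% / 43% | 40% / 52% |
| 0.35 | 57% / 72% | 68% / 82% |
| 0.25 | 75% / 90% | 87% / 96% |

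For example, at HR 0.35 with 16 events: √4·1.050 − 1.645 = 0.455, and Φ(0.455) = 0.68. The panel rates track the power of response, which is what a re-test of response would produce.

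**3. Sensitivity.**
- At HR 0.35 and 20 events, varying panel size (5 to 50), marker count (200 to 20,000), penalty and response rate (30%) gives 49% to 75%.
- An elastic net on 5,000 noise markers with about 44% responders and 30% events (0.30·64 ≈ 19) gives 27% to 36% at HR 2 and 44% to 62% at HR 3 (non-responder v responder).
- A run with 3,000 noise markers and 20 events gives 26% to 40% at HR 2 and 46% to 65% at HR 3.

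**4. The other reading of the panel score.** With an unweighted sum of squared Z scores over the selected markers (2,000 noise markers, 5 or 20 kept, 20 events, mean Z of 0, 1 or 2), the rate is 6% to 20%. A separate run reached 22%.

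**5. The TRG-adjusted step.** With TRG entered as the same binary response used in the fit, the in-sample score gives p < 0.1 in 9% to 12% of runs (up to 13.5% in the sensitivity settings). Requiring univariate p < 0.1 and then p < 0.05 (the level given under Other study parameters) leaves 2% to 4% with TRG alone, and 2% to 6% with TRG plus six further covariates.

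**6. Comparators.**
- Out-of-fold panel scores in the same patients: 10% to 16% (10-fold, ridge) and 9% to 15% (5-fold, elastic net).
- Panel scores in new patients: 10% to 12%.
- Genome-wide score: 8% to 13%.

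**The case against.** The strongest reply is that the plan already contains the correction. A univariate hit is followed by a model that includes TRG, the variable that drives the artefact. This stands. A reader might infer that the plan will often end by declaring noise markers associated with survival. It does not support that, because only 2% to 6% of noise panels pass both steps. What remains is that the univariate result is itself labelled significance and answers the stated question first. The adjusted model answers a different one, namely whether the panel adds to TRG. With a correlation of 0.89, the in-sample score enters that model with a variance inflation of roughly 1/(1 − 0.89²) = 4.8, so a real effect would be hard to see.

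Second, no fitted linear score is named for the Cox model, and the sum of squared Z scores is the only summary score defined. This also stands: under that reading the problem is small to modest. The wording does not settle which score is meant.

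Third, in-sample scoring is not stated, and cross-validation may be described in the full protocol or the cited method. That is fair. The point is therefore conditional on an in-sample score.

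Fourth, the analysis is exploratory and external validation is foreseen. The validation under Primary study parameter(s) is described for the panel that predicts response, with no mention of RFS or OS. An exploratory label lowers the stakes but does not change what the test measures.

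A reader might also infer that watch-and-wait patients, whose scores would be out-of-sample, are mixed with resected patients in one Cox model. The Statistical analysis section keeps them separate, so that does not follow.

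**Conclusion.** The concern holds for the univariate panel result only, and only if the panel enters as a score fitted and evaluated in the same patients. With assumed response–RFS hazard ratios of 2 to 3 and about 20 events, noise panels reach p < 0.1 in roughly 25% to 65% of studies instead of 10%. With an unweighted sum of squares the rate is about 6% to 20%. At a hazard ratio of 0.7 it is 16% to 19% for the fitted score, and with no response–survival link there is no excess. The genome-wide score is unaffected, and the TRG-adjusted step largely removes the problem.

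The size rests on assumed hazard ratios, event counts, response rate and panel size, on independent markers, and on simple stand-ins for the cited method. Correlated markers would change the size but not the direction. The matter is worth correcting, at moderate weight for an exploratory analysis.

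**What to change.** Under Secondary study parameter(s):

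1. State which panel score enters the Cox models (fitted weighted score or sum of squared Z scores).
2. Use out-of-fold panel scores. Repeat the whole selection and weighting described under Primary study parameter(s), including the response-based tissue contrasts, inside each cross-validation fold. Score each resected patient from the model fitted without that patient.
3. Base any statement that the panel is associated with RFS or OS on the out-of-fold score and the TRG-adjusted result, not on an in-sample univariate p < 0.1.
4. Leave the genome-wide score analysis and the separate handling of watch-and-wait patients as they are.

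Out-of-fold scoring brings the error rate close to nominal rather than exactly to it (9% to 16% across the settings above). The cost is wording and some computing time, with noisier and less favourable panel hazard ratios. No patients, samples or assays are added.

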### Other study parameters

In an exploratory analysis we will investigate the methylation profile and treatment response with known clinical risk factors and patient characteristics. Multivariate regression analysis will be performed and also RFS and OS will be measured. Significance is determined to be (p < 0.05). Demographics and baseline characteristics will be summarized descriptively. Descriptive statistics will include median and interquartile range or mean and standard deviation for continuous variables, and frequency counts with percentages for categorical variables. Demographics and baseline characteristics will be summarized.

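### The adjusted RFS/OS Cox model is fitted only after a univariate p < 0.1, so the adjusted hazard ratios that get reported are selected and exaggerated

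*Protocol article*

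**What the plan says.** The Protocol article, under Secondary study parameter(s), plans "univariate Cox regression analyses with the resulting methylation summary score for the entire profile as well as the selected marker panel", the codings being "both continuous and dichotomized on the median". The outcomes are the "secondary outcome measures Recurrence Free Survival (RFS) and Overall Survival (OS"). The adjusted model is conditional: "In case of significance (p < 0.1) for the univariate analysis subsequently a multivariate model will be built using known risk factors". The listed factors number seven, "including clinical (TNM stage, tumour location, age, gender), and pathological (differentiation grade, microsatellite instability status, TRG) parameters". The section introduces all of this as exploratory: "In an exploratory analysis we will investigate whether the obtained methylation profiles are associated with our secondary outcome measures".

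It does not say which univariate test has to pass, or whether one pass opens the adjusted model for every score and outcome. The later of the two sections headed Other study parameters mentions multivariate regression and adds "Significance is determined to be (p < 0.05"). It says RFS and OS will be measured, but does not clearly commit to an adjusted survival model regardless of the univariate result.

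**The concern.** The variable being screened is the one of interest. If the adjusted model is fitted only when the methylation score already shows a large enough univariate effect, every adjusted hazard ratio that exists comes from a selected data set. A reader who sees that hazard ratio with its confidence interval will take it as an ordinary estimate, although the rule pushes it away from 1. With several scores, codings and outcomes, the gate also has several chances to open when nothing is there. Conversely, no adjusted estimate is produced when the univariate effect is weak, even if adjustment would have strengthened it. This is a rule that the plan states, so following it exactly produces the problem.

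**Working it through.** **Inputs from the article.** Gate p < 0.1 (taken as two-sided; not stated). Scores: 2. Codings: 2. Outcomes: 2. Listed covariates: 7. At least 64 evaluable patients and 75 enrolled (Sample size calculation, which concerns response, not survival). No event count, follow-up length or power is given for RFS or OS, so there is no planned figure to reproduce, and all event counts below are assumptions.

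**Number of tests.** 2 × 2 × 2 = 8. If the two codings apply only to the panel, (1 + 2) × 2 = 6.

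**Chance that the gate opens with no true effect.**
- Any single test: 10%.
- Independent tests: 1 − 0.9^8 = 57% for eight and 1 − 0.9^6 = 47% for six. These are only upper references, because the codings and the two outcomes are correlated.
- Simulated, 64 patients, 20 RFS and 12 OS events, score correlation 0 to 0.8, 600 runs per setting: at least one of eight passes in 35-45%.
- Simulated, 64 or 75 patients, on average about 19-22 RFS and 13-15 OS events, score correlation 0 to 0.95, 6,000 runs per setting: 29-41%. Within one outcome (four tests): 20-29%.

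**Why the passing estimate is exaggerated.** For a score standardised to SD 1 with d events, the standard error of the log hazard ratio is about 1/√d. The smallest harmful hazard ratio that passes is therefore exp(1.645/√d):
- d = 12: exp(0.475) = 1.61
- d = 20: exp(0.368) = 1.44
- d = 25: exp(0.329) = 1.39

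For a median split the standard error is about 2/√d, and the threshold at d = 20 is exp(1.645 × 2/√20) = 2.09. So with up to 25 events a univariate estimate equal to a true 1.3 per SD cannot pass; only overestimates do.

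**Carry-over to the adjusted hazard ratio.** Simulated, 64 patients, one continuous score with its own gate, true hazard ratio 1.3 per SD:

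| Assumed events | Adjusted model always fitted | Only when passed, harmful direction |
|---|---|---|
| 15-25 (mean, 2 or 4 covariates) | 1.32-1.34 | 1.65-1.94 |
| 12-20 (median) | 1.31-1.35 | 1.68-2.29 |

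A further set with 15-25 events gave 1.63-1.83 when passed. The overall range is roughly 1.6-2.3.

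**Type I error.** For one model, passing the gate and then having adjusted p < 0.05 is a subset of having adjusted p < 0.05, so the gate cannot raise the unconditional rate. Simulated: 3.8-5.8% gated, 4.4-7.0% ungated. Given that the gate has passed, the adjusted test is below 0.05 in 33-51% of null studies. That follows largely from the selection, since about half of null p-values below 0.1 are also below 0.05.

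**Missed adjusted effects.** Simulated, 75 patients, about 20 events, true adjusted hazard ratio 1.6 per SD, risk-factor hazard ratio 1.8, one gate, 600 runs per setting:

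| Score-covariate correlation | Found at p < 0.05, no gate | Found with gate |
|---|---|---|
| 0 | 50% | 48% |
| −0.3 | 48% | 31% |
| −0.5 | 43% | 20% |

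**The case against.** The strongest reply is that the analysis is labelled exploratory, that the study has no clinical consequences for its patients (Objectives), and that implementation of an assay awaits external validation. No decision rests on the adjusted survival model. This stands and limits the severity, but the label does not correct a selected estimate.

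Several stronger readings are tempting and are not supported:
- A reader might infer that the gate inflates the false-positive rate. For a single model it does not. The 33-51% figure is conditional on passing and should not be quoted as a type I error.
- A reader might infer that real adjusted effects will often be missed. That needs negative confounding between the score and a risk factor, which nothing in the article suggests. At zero correlation the loss is about 2 points.
- A reader might combine the chance opening over eight tests with the missed effects from a single gate. They belong to different readings of the rule. If any of eight passes suffices, fewer effects are missed. If each model has its own gate, chance opening is about 10% per model.
- A reader might see the 0.1 and 0.05 levels as a contradiction. They stand in different sections, and 0.1 serves as a screen for model building, so this is at most loose wording.
- Nor does the article say that the univariate results will go unreported; they are planned unconditionally.

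It is also fair to object that simply deleting the gate and always fitting all seven listed factors would be poor. With the score that is at least 8 parameters, or 12/8 = 1.5 to 20/8 = 2.5 events per parameter. In simulation with seven covariates, the ungated type I error was 7.6% at 12 events and 6.5% at 20. The fix has to deal with this.

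**Conclusion.** The point holds as one of selective, exaggerated reporting. Followed as written, the rule yields an adjusted hazard ratio only in studies where the univariate effect is already large. Under the assumed 12 to 25 events, a true 1.3 per SD is then seen as roughly 1.6-2.3, against about 1.3 if the model were always fitted. With no true effect, at least one of the eight tests opens the gate in roughly 30-45% of studies if any pass counts. Possible loss of an adjusted effect is a secondary concern that depends on negative confounding and is negligible without it. The sizes rest on assumed event counts, score correlations and covariate effects; the direction of the bias does not. Severity is minor to moderate, because the analysis is secondary and exploratory.

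**What to change.** Delete the p < 0.1 condition. For each of RFS and OS, name one continuous methylation score and report its adjusted Cox hazard ratio with 95% CI whatever the univariate result. Replace the full list of seven factors with a short pre-specified covariate set limited to what the observed events support, or use penalised estimation. Report all univariate results, for every score, coding and outcome, and label them exploratory.

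The cost is a change of wording; no new patients, samples or procedures are needed. The downsides are that a null adjusted result is also reported and that fewer covariates are adjusted for.
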